## Abstract

**Background:** Advanced treatment options for non-small cell lung cancer (NSCLC) consist of immunotherapy, chemotherapy, or a combination of both. Decisions surrounding NSCLC can be considered as preference-sensitive because multiple treatments exist that vary in terms of mode of administration, treatment schedules, and benefit–risk profiles. As part of the IMI PREFER project, we developed a protocol for an online preference survey for NSCLC patients exploring differences in preferences according to patient characteristics (preference heterogeneity). Moreover, this study will evaluate and compare the use of two different preference elicitation methods, the discrete choice experiment (DCE) and the swing weighting (SW) task. Finally, the study explores how demographic (i.e., age, gender, and educational level) and clinical (i.e., cancer stage and line of treatment) information, health literacy, health locus of control, and quality of life may influence or explain patient preferences and the usefulness of a digital interactive tool in providing information on preference elicitation tasks according to patients.

**Methods:** An online survey will be implemented with the aim to recruit 510 NSCLC patients in Belgium and Italy. Participants will be randomized 50:50 to first receive either the DCE or the SW. The survey will also collect information on participants' disease-related status, health locus of control, health literacy, quality of life, and perception of the educational tool.

**Discussion:** This protocol outlines methodological and practical steps to quantitatively elicit and study patient preferences for NSCLC treatment alternatives. Results from this study will increase the understanding of which treatment aspects are most valued by NSCLC patients to inform decision-making in drug development, regulatory approval, and reimbursement. Methodologically, the comparison between the DCE and the SW task will be valuable to gain information on how these preference methods perform against each other in eliciting patient preferences. Overall, this protocol may assist researchers, drug developers, and decision-makers in designing quantitative patient preferences into decision-making along the medical product life cycle.

## Introduction

Lung cancer (LC) is the most prevalent and deadliest cancer worldwide with at least 85% of them affected by non-small cell lung cancer (NSCLC) (1). Late diagnosis is one of the fundamental reasons for the high number of deaths, with more than 70% of new cases detected too late for trying curative treatments (2). Moreover, NSCLC patients are a vulnerable population both because most patients with a diagnosis of LC are 65 or older and because they reported high levels of physical and psychological distress and suffering (3).

In the last few years, patient preference (PP) for treatment outcomes has been receiving increasing attention as a relevant source of complexity (4–6). Specifically, PP heterogeneity arises when patients differ in how they value specific treatment attributes or outcomes. Treatment options for NSCLC may vary widely according to disease stage. Traditionally, treatment options for advanced-stage NSCLC have consisted of chemotherapy, radiation therapy, or a combination, whereas surgery is a more feasible treatment option for the early stage. However, the current treatment paradigm for advanced-stage NSCLC has shifted due to the development and introduction of drug therapies with novel mechanisms of actions. In particular, immunotherapy with immune checkpoint inhibitors (ICIs) has been developed (7, 8).

Nevertheless, without clinical trials comparing different NSCLC treatment options, there is no clinical evidence that allows to determine a clinically superior treatment for advanced stage patients. Further, NSCLC treatments (including immunotherapy and chemo-immunotherapy) have different treatment characteristics that may influence treatment decisions. NSCLC treatments vary in terms of mode of administration, treatment schedules, and benefit–risk profiles. For instance, while chemo-immunotherapy is administered as an intravenous infusion lasting at least 4–5 h, immunotherapy has a much shorter infusion time of about 1 h. Toxicity profiles also differ between NSCLC treatments. For example, chemotherapy can carry both acute and late toxicities; while the former includes nausea, vomiting, paresthesia, anemia, fatigue, and fever, the latter can include persistent neurotoxicity and infertility. However, immunotherapy is typically better tolerated, as the most common side effects are rash, itch, mild diarrhea, fatigue, and subclinical thyroid dysfunction. Therefore, in view of the existence of multiple treatments with varying modes of administration, treatment schedules, benefit–risk profiles, no clinical superior treatment, and treatment options that vary widely according to disease stage and severity (9), PP may play a pivotal role in understanding the relative value of different therapeutic options and their attributes for NSCLC patients. Decisions concerning NSCLC treatment can be considered a PP-sensitive decision, and a better understanding of the patient's experience with NSCLC is therefore pivotal in these circumstances. For example, NSCLC patients have a low life expectancy that varies according to the disease stage (10), and the understanding of their preference regarding treatment options, the maximum acceptable risk (MAR), and the minimum acceptable benefit (MAB) they would be willing to accept for treatment alternatives may inform stakeholders.

A recent systematic review suggested that, alongside socio-demographic (e.g., age) and clinical characteristics (e.g., disease stage), patients' psychological aspects (e.g., health literacy and health locus of control) may have an impact on PP and health-related decisions (11). However, since no empirical evidence is reported on how these psychological aspects may affect preferences of LC patients for their treatments, based on the perspective of personalized medicine (12–14), this information would be essential to propose and deliver personalized treatments for NSCLC.

PP can be elicited through various quantitative techniques. DCE is the most common method for eliciting PP in the life cycle of medical products (15). It is a quantitative method to assess PP by asking respondents to state their choice over sets of hypothetical alternatives defined by different levels of several characteristics, known as attributes. These responses are then considered to infer the value placed on each attribute. These responses are then considered to estimate the strength of preference for change in levels of considered characteristics (16). Another quantitative preference method that has gained attention is swing weighting (SW), which has emerged during the last years as an alternative method for eliciting PP (17). SW asks respondents to indicate which attribute they would prioritize to improve from the worst to the best.

SW and DCE are two widely used PP methods in the field of health. Notwithstanding, research directly comparing DCE and SW is particularly lacking (18, 19). Methods such as SW that do not force patients' simultaneous trade-offs between multiple attributes (20) are considered simpler. Otherwise, others suggested that direct comparisons in a DCE can be easier for patients (18). Therefore, the aim of this study is to compare the performance and results of DCE and SW in a common preference context through empirical research.

Even if there are conceptual, methodological, and practical differences between DCE and SW, there is limited empirical evidence on how the SW and DCE perform against each other in eliciting PP. From a methodological stance, it would therefore be relevant to evaluate and compare these two different methods in eliciting PP for NSCLC treatments.

### Study Objectives

This study is part of the Innovative Medicines Initiative (IMI) Patient Preferences in Benefit-Risk Assessments during the Medical Product Lifecycle (PREFER) project (21). This 5-year research project will develop evidence-based recommendations to guide industry, regulatory authorities, and health technology assessment bodies on when and how PP on benefits and harms should be assessed and used to inform decision making throughout the medical product life cycle (for a brief overview, see https://www.imi-prefer.eu/ or https://www.imi.europa.eu/projects-results/project-factsheets/prefer).

This study has both clinical and methodological endpoints. The clinical endpoints of this study are:

What are the MAR and MAB that patients would accept for treatment alternatives?What are the clinical, demographic and psychological variables that may explain patients' preferences? In particular, we will explore to what extent PPs vary with disease stage and line of treatment, age, gender, educational level, and psychological characteristics of the patients (i.e., health literacy and health locus of control).

As methodological endpoints, the study will assess the following:

How similar are the results acquired from the two different methods (i.e., DCE and SW) applying the same set of attributes on the same population? To what extent assessing preferences for treatment alternatives in NSCLC patients with a DCE will provide comparable information if compared to a different method like the SW? The aim is to highlight the strengths and weaknesses of two different methodologies in identifying and profiling different treatments within the context of patient management.Would an educational tool be perceived as being a useful way to provide information on treatment attributes and attribute levels, and to teach participants how to perform different choice tasks?

## Methods

### Design

This study will be implemented following the International Society for Pharmacoeconomics and Outcomes Research (ISPOR; 22) guidelines for eliciting preferences and conducting PP studies. It is a cross-sectional study consisting of an online survey administered to NSCLC patients in Belgium and Italy. The NSCLC participants will be randomized 50:50 to first receive either a DCE or SW task. This is to avoid order effects that could introduce confounding. Before completing the DCE and SW tasks, patients will receive a description of the attributes included in the two choice tasks and instructions about how to complete each task using an educational tool.

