### Participants

The study aims to recruit 510 NSCLC patients from three cancer treatment centers (*N* = 170 per center) in Italy (*N* = 340) and Belgium (*N* = 170). Italian patients will be recruited at the European Institute of Oncology and the National Institute of Cancer in Milan. Belgian patients will be recruited at the Respiratory Oncology Department and the Department of Thoracic Surgery of the KU Leuven University Hospital in Leuven. Each cancer center treats approximately 500 NSCLC patients yearly. NSCLC patients in different stages (stages I–IV) will be recruited and divided into two groups (see Figure 1): 255 early stages (stages I and II) and 255 later stages (stages III and IV).

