### Sample Size Estimation

For SW, no specific sample size is required since the sample size does not depend on the magnitudes of the utility differences (22). Therefore, the sample sizes will be dictated by requirements for the DCE. To the best of our knowledge, there are no statistical tools able to estimate the sample size for a DCE. Therefore, we referred to the literature to estimate the sample size for the present research. Most published choice experiments have a sample size of between 100 to 300 respondents (23). However, according to Bekker-Grob et al. (24), the minimum sample size depends on several criteria, including the question format, the complexity of the choice task, the desired precision of the results, and the need to conduct subgroup analyses (25, 26). Given this, we have determined that, based on the sample size requirements for both methods and taking into account the number of research questions this study anticipates to answer, a sample size of 510 respondents (170 per site) is expected to provide enough information to identify preferences in each country and comparisons across countries and disease groups with acceptable precision.

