### Statistical Analyses

The clinical objective of this study is to assess patients' preferences for relevant treatment attributes related to LC treatment alternatives. To determine preferences of study participants, attribute (level) estimates and the conditional relative importance of attributes will be explored in the DCE using conditional logit models. For the final analyses, preferences for attributes of NSCLC treatment random parameters logit (RPL) modeling and latent class analysis (LCA) will be considered. Final decisions on the modeling procedure will be made once data collection has been completed and explored. This decision will be based on model fit and clinical interpretation. Different models might be used to answer the different research questions in this case study. Heterogeneity of preferences and the impact of participant characteristics among which psychological variables will be investigated *via* LCA or subgroup analyses using RPL.

For the SW, each attribute is first ranked by the participants, and then the relative importance is indicated through point allocation. The rank order will be turned into weights using a rank-to-weight method, rank order centroid method (35). Using this approach, the average weight per attribute over the entire group of respondents is then calculated and it becomes possible to statistically investigate whether weights differ between subgroups.

The MAR and MAB values for benefits and risks of interest will be determined based on DCE outcomes.

The methodological objective of this study is to evaluate the similarity of DCE and SW in assessing preferences for treatment alternatives in NSCLC. The results of the DCE and SW will be compared qualitatively and quantitatively to evaluate whether the results are different when applying two different methods. As a first step, validity checks, completion time (through log information), dropout, and response to feedback questions will be compared between the two methods. Second, the relative importance of the included attributes will be compared between the two methods.

PP heterogeneity and the influence of participants' clinical (i.e., disease stage and line of treatment), socio-demographic (i.e., age, gender, and educational level), and psychological characteristics (i.e., health literacy and health locus of control) will be investigated by applying appropriate statistical models including LCA and/or subgroup analyses.

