### Handling Missing Data

Respondents who choose not to answer certain demographic or treatment history questions will be noted in the summary statistics, and their responses will be included in the DCE; however, if data required to assign an individual to a subgroup are missing, that individual will be excluded from the subgroup analysis (pairwise deletion). Respondents who do not answer at least one DCE question and at least one SW question in the survey, or who always select the same alternative (either treatment A or treatment B) in all of the DCE questions (“flatliners”), will be analyzed separately as a part of the quality assessment evaluation. For comparing DCE to SW, we will include respondents who fully completed both methods, whereas for the separate analyses on the DCE or SW, we will include respondents that completed parts of the methods.

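### Balancing task order does not remove anchoring of the second task on the first, and the DCE–SW comparison, fixed to completers of both tasks, names no analysis by order

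*Protocol article*

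**What the plan says.** - **Allocation (Design).** "The NSCLC participants will be randomized 50:50 to first receive either a DCE or SW task". The stated purpose is: "This is to avoid order effects that could introduce confounding".
- **Size (Participants).** "The study aims to recruit 510 NSCLC patients from three cancer treatment centers", at 170 per centre. A 50:50 split gives 255 per task order.
- **Method comparison (Statistical Analyses).** As a first step, "validity checks, completion time (through log information), dropout, and response to feedback questions will be compared between the two methods". Then: "Second, the relative importance of the included attributes will be compared between the two methods". Task order is not mentioned in either step. It is also absent from the heterogeneity factors, which are clinical, socio-demographic and psychological.
- **Comparison set (Handling Missing Data).** "For comparing DCE to SW, we will include respondents who fully completed both methods". Partial responders are kept only for the separate DCE and SW analyses.
- **Model choice (Statistical Analyses).** "Final decisions on the modeling procedure will be made once data collection has been completed and explored".

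Two further points matter. Attributes and Levels Development gives both tasks identical attributes and levels. Study Objectives asks how similar the results of the two methods are when the same attributes are put to the same population.

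**The concern.** The methodological endpoint is similarity between two methods that each patient completes in succession, on the same five attributes. A patient who has settled in the first task that survival matters most can carry that answer into the second. Agreement between the DCE and the SW may then partly reflect the first task being repeated, rather than two methods independently recovering the same preferences.

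Randomising the order protects against one kind of order effect and not against this one. The plan relies on balance alone, and its comparison set consists entirely of people who did both tasks. Every comparison in that set therefore includes second-task data. Patients who finished their first task and then left are excluded from it, although their data are free of carry-over. The Discussion says the results will feed into international recommendations on preference methods, so agreement inflated by carry-over would have consequences beyond this study.

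**Working it through.** **Figures in the article.** 3 × 170 = 340 + 170 = 255 + 255 = 510, which agrees throughout. There is no power calculation to reproduce, because Sample Size Estimation rests on published practice ("Therefore, we referred to the literature to estimate the sample size for the present research"). All effect sizes below are therefore assumptions. They are in SD units, with a correlation of 0.5 assumed between the two tasks, so that the within-person difference also has SD 1.

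**1. General two-sequence result.** Let n1 be the completers who did the DCE first and n2 those who did the SW first. Let π be a second-position effect common to both tasks, cD the carry-over onto the DCE after the SW, and cS the carry-over onto the SW after the DCE. The DCE − SW difference is biased by −(π + cS) in the first group and by +(π + cD) in the second. The pooled bias is

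[n2(π + cD) − n1(π + cS)] / (n1 + n2).

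**2. What balance cancels.** With 255 v 255:
- π = 0.2 and no carry-over: bias 0.
- π = 0.2 and cD = cS = 0.1: bias 0.

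Ignoring a common π costs only precision. The SD of the difference becomes √(1 + π²), which is 1.02 at π = 0.2 and 1.12 at π = 0.5.

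**3. What balance does not cancel.** With equal groups the bias reduces to (cD − cS)/2.
- cD = 0.2, cS = 0: bias 0.10.
- cD = 0.2, cS = −0.2: bias 0.20.

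**4. Anchoring is the second of these patterns.** Let D and S be the importance of an attribute from each method when done first, on a common scale. Let the second answer be pulled a fraction L towards the first.
- DCE first: D − [(1 − L)S + LD] = (1 − L)(D − S).
- SW first: [(1 − L)D + LS] − S = (1 − L)(D − S).

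Here cD = L(S − D) and cS = L(D − S), equal and opposite. The difference shrinks by L in both orders whatever the split, so 50:50 allocation offsets none of it. For assumed L of 0.1, 0.3 and 0.5 the understatement is 10%, 30% and 50%.

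Both orders show the same shrunken difference, so an order term fitted to the paired difference alone would not reveal anchoring. Order has to be examined within each method, or the first tasks compared directly.

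**5. Unequal completion.** With π = 0.2 and no carry-over:
- 95% v 80% completing (242.25 v 204): 0.2 × (204 − 242.25)/446.25 = −0.017.
- 95% v 60% completing (242.25 v 153): 0.2 × (153 − 242.25)/395.25 = −0.045.

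**6. Feasibility of a first-task comparison, 255 v 255, two-sided alpha 0.05 (assumed).** Power is 0.62, 0.81 and 0.92 for differences of 0.20, 0.25 and 0.30 SD. The detectable difference is (1.96 + 0.84) × √(2/255) = 0.25 SD at 80% power and 0.29 SD at 90%. The standard error is √(2/255) = 0.089, against 1/√510 = 0.044 for the paired comparison if everyone completes: twice as large. These figures treat importance as a patient-level score. DCE importance comes from a choice model, so they are a guide only.

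**The case against.** The strongest reply has four parts.

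**The full plan is not shown.** This is a condensed article, and order terms or first-task sensitivity analyses are often left to the analysis plan. That stands as far as it goes. A reader might infer that the orders will be pooled and order never examined, but the article does not say so, and it leaves modelling open. The point rests instead on two things that are written: a purpose that balance alone cannot fully meet, and a comparison set confined to completers of both tasks.

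**Balance does its job on practice.** A reader might also infer that practice stays mixed into the DCE–SW contrast. It does not: with equal groups, a practice or fatigue effect common to both tasks cancels on average. The educational tool, with practice tasks given beforehand, should reduce it further. Neither the balance nor the tool deals with anchoring.

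**The size is unknown.** Nothing in the article shows that anchoring occurs or that completion will differ by order. The completion biases in step 5 are also below the standard error of the paired comparison (1/√446.25 = 0.047 and 1/√395.25 = 0.050). This is a fair limit on severity. Anchoring is different in kind: it shrinks the difference proportionally and a larger sample does not help.

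**The first-task comparison should not take over.** It is between groups and about half as precise, so a disagreement with the paired result could be noise. This is accepted, and the first-task comparison is proposed as a sensitivity analysis only.

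**Conclusion.** The point holds in limited form. Randomised order removes a position effect common to both tasks. It does not remove anchoring or asymmetric carry-over, and its balance is not guaranteed among completers. Anchoring would bias the similarity endpoint towards agreement by the fraction L; the 10% to 50% range rests on assumed values of L and a linear pull towards the first answer. Other asymmetric carry-over could bias the comparison in either direction, by half the difference between the two carry-over effects.

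It would go too far to conclude that the planned comparison is invalid or that the first-task result must replace it. No stated figure is wrong, no sections contradict each other, and the sample size is unaffected. This is a worthwhile, low-cost strengthening of the plan rather than a defect that must be cured before the study can proceed.

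**What to change.** Keep the paired comparison of completers as planned, and add:

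1. **A prespecified sensitivity comparison** of first-task DCE with first-task SW between the randomised order groups, on relative importance expressed on a common scale, using everyone who completed their first task, whether or not they went on to the second.
2. **An order term in each method's own analysis**: interactions of order with the attributes in the DCE model (a respondent-level term alone drops out of a choice between two options), and order in the comparison of SW weights.
3. **Completion, dropout and completion time reported by order.** Dropout in particular depends on which task came first, and it cannot be assessed among full completers.

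If the first-task and paired results differ materially, report both and qualify the similarity conclusion, without switching automatically to the first-task result. Reword the Design section to say that order is balanced between the methods, not that order effects are avoided.

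The cost is some wording and a few extra analyses. No new data or patients are needed. The drawback is the lower precision of the first-task comparison, which should be stated alongside its result.
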